### Statistical analysis

Intention-to-treat (ITT) and per protocol (PP) analyses will be conducted. The ITT population will include all subjects who are randomised whereas the PP population will include those subjects who received 90% allocated treatment. The primary outcome measure (ARAT at the end of intervention at 6 weeks) will be analysed using analysis of covariance fitted within a Generalised Linear Mixed Model (GLMM) framework to adjust for the repeated measurements on individuals. The outcome in the model will be the individual’s ARAT (immediately after 6 weeks of intervention/6 months after intervention commencement); fixed effects in the model will be group, time and the interaction of time by group, baseline ARAT score and stratification variables (site and severity of upper limb impairment). A random effect for subject will be included. Secondary outcome measures of MAL, WMFT, FMA, EQ5D-5 L, CSI, and mRS will be analysed using the same approach as used to test the primary outcome, with appropriate distributional families depending on the type of outcome. Pre-specified sub-group analysis: We will conduct sub-group analyses to determine differential effects of the intervention in participants with voluntary finger extension (no extension, partial, or full extension) at 3 months post stroke. The GLMM regression model described above will be fitted within each of the sub-groups. No formal tests of significant interactions will be assessed for these models, since the study is not powered for these tests. The primary analysis will take place when follow-up is complete for all recruited participants. No formal interim analysis is planned.

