### Data collection

Data will be collected and stored using a web-based database REDCap, hosted by HMRI on a secure server. After giving consent, a baseline assessment will be conducted for the participant. As well as the outcome measures, demographic data will be collected at baseline including:

Whether thrombolysis or clot retrieval was used (if this information is available)National Institute of Health Stroke Scale (NIHSS)Assessment of upper limb sensory deficit including proprioception (Wrist Position Sense Test (44)) and touch (Tactile Discrimination Test (45))Ability to perform voluntary finger extension (within the Fugl-Meyer Assessment, by test item 25 -‘extend all fingers’)The Montreal Cognitive Assessment (MoCA) (46), a rapid screening instrument for mild cognitive dysfunction. It assesses different cognitive domains: attention and concentration, executive functions, memory, language, visuoconstructional skills, conceptual thinking, calculations, and orientationSelf-efficacy using the Stroke Self-Efficacy Questionnaire (47)Depression using the Hospital Anxiety and Depression Scale (HADS) (48) or the Stroke Aphasic Depression Questionnaire (SADQ) (49). To determine which of these scales is used, language is assessed using the Sheffield Screening test for Language Disorders (receptive language subsection) (50). If the participant scores less than 9 out of 9 on the receptive subsection, the SADQ is administered, instead of the HADSPresence of vascular risk factors, comorbid conditions such as cognitive decline, arthritis and renal disease, other neurological disease, and type of stroke -ischaemic/haemorrhagic, lacunar/large artery/other, cortical/subcortical, whether thrombolytic drugs were used, side of hemiplegia, handedness whether able to walk independently at stroke onset, and whether active hand movement was present at stroke onset.

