### Sample size

We aim to detect a minimal clinically important difference of 5 points on the ARAT, which derives from findings of van der Lee et al. (51), who reported a difference of 5.7 for a mildly impaired population. The clinically important mean change for the ARAT for different severity groups are not yet published. We have adjusted to 5 to reflect the inclusion of moderate to severe impairment in our expected population, [our previous feasibility study population included 37% participants with severe (i.e., ARAT 0–3) impairment] (17). Based on observed values from our feasibility study, i.e., a pooled standard deviation on the ARAT of 18 and a correlation between baseline and follow-up of 0.72, 300 participants (150 per group) will provide the study with 80% power to detect the 5 point change on the ARAT at the 5% significance level (two-tailed test), allowing for a 20% loss to follow-up. Using similar assumptions, the study would have 80% power to detect differences between groups of 0.3 SDs on the WMFT, MAL, and the Caregiver Strain Index.

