### Limitations to the study

In this study protocol, it is acknowledged that in making certain considered choices regarding our research plan, these choices, however well-reasoned, may give rise to other potential limitations, so we would like to note these here. Firstly, we chose to use a broad-based inclusion criteria, in order to make our results applicable to the wider stroke population. So we decided not to exclude people with no finger extension at time of recruitment, neglect/inattention and dyskinesia. The presence of these factors may impede the effects of rehabilitation, but since we were not aware of evidence that task-specific training might not still work with these people, we allowed them to be included. Secondly, for those participants with low baseline scores on the ARAT or no finger extension at the time of recruitment, which would be predictive of poor upper limb recovery, it could be argued that these participants could be closely monitored with more frequent assessments, in order to ascertain whether continuation of therapy is justified. To deal with potential limited recovery of finger extension, in this study we have included two other assessments as well as the ARAT, namely the WMFT and the FMA, which allow improvements to be measured in other movements involving the shoulder, elbow and wrist, even if finger extension has not recovered. However, in planning future studies, it would be good to include a mechanism to justify continuation of therapy. Thirdly, due to finite resources, which were under further pressure due to the effects of Covid, it was not possible to periodically check the fidelity of each individual assessor’s assessment technique, after their initial competence was checked after training. Assessors did receive a thorough training for their role, including supervised assessments with participants. Additional tutorials on the FMA and WMFT were held by zoom as needed, video materials of these assessments being done with patients and scores were provided for extra practice/confirmation and the trainers were made available to assessors for further input when requested. Also, when assessments were returned to the trial manager, they were thoroughly checked and any anomalies followed up. However we acknowledge that periodic checking of assessor technique is desirable in future trials.

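### The primary ARAT model leaves out baseline finger extension, which the protocol itself calls predictive of recovery; adding it could gain some precision

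*Protocol article*

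**What the plan says.** All places are in the protocol article.

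- **Statistical analysis** names the fixed effects of the primary model: "fixed effects in the model will be group, time and the interaction of time by group, baseline ARAT score and stratification variables". A random subject effect is added. Finger extension (none, partial or full) appears in this section only as the pre-specified subgroup factor, and the same model is refitted within each level.
- **Limitations to the study** refers to "low baseline scores on the ARAT or no finger extension at the time of recruitment, which would be predictive of poor upper limb recovery". Finger extension is thus named next to the ARAT as a prognostic factor.
- **Data collection** lists "Ability to perform voluntary finger extension" among the baseline items (Fugl-Meyer item 25). **Study methods** places randomisation after the baseline assessment, and stratifies by ARAT severity and state but not by finger extension.
- **Sample size** says "300 participants (150 per group) will provide the study with 80% power", for a 5-point ARAT difference, with SD 18, baseline-to-follow-up correlation 0.72 and 20% loss.
- **Modifications due to Covid-19** reports that 100 participants is now the realistic expectation.

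**The concern.** The protocol identifies two baseline markers of poor recovery and uses only one of them to reduce error in the primary comparison. The other is already in the dataset, is fixed before allocation, and was judged important enough to be the only pre-specified subgroup factor. Because the fixed effects are listed explicitly, leaving it out is a stated choice and not a gap left for the analysis plan.

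At stake is efficiency. Any outcome variance that finger extension explains beyond the ARAT stays in the residual. At 300 participants there is room for that. At 100, power for the target difference is well under one half, so precision from data already collected has more value. There is also a reason why the ARAT may not carry all the information: the feasibility sample had 37% of participants at ARAT 0–3, and within so narrow a band neither the continuous score nor the stratum can separate participants much.

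**Working it through.** **Inputs from the documents.** Difference 5 points, SD 18, correlation r = 0.72, two-sided 5%, 20% loss, 1:1 allocation; 300 planned, 100 now expected. Evaluable per arm: 150 × 0.8 = 120 and 50 × 0.8 = 40.

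**Input not in the documents.** The extra share of ARAT variance that finger extension explains beyond baseline ARAT and severity. A range of 0.02 to 0.10 is assumed.

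**Step 1: the plan's own figure.**
- Change score: SD = 18 × √(2 × (1 − 0.72)) = 13.47. With 120 per arm, power is 82%. The required total is 114 per arm, or 286 after inflation for loss. The stated 300 at 80% is consistent with this.
- Planned analysis of covariance: R² = 0.72² = 0.518; SD = 18 × √(1 − 0.518) = 12.49. With 120 per arm, power is 87%. The required total is 98 per arm, or 246 after inflation.

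So the stated power is conservative for the planned model, without finger extension.

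**Step 2: add finger extension, with the range read as an increment to total R².** SE = 18 × √(1 − R²) × √(2/n); power from the noncentral t distribution.

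| Added R² | R² | Residual variance falls by | Equivalent to extra participants | Power, 40 per arm | Power, 120 per arm |
|---|---|---|---|---|---|
| 0 | 0.518 | – | – | 42% | 87% |
| 0.02 | 0.538 | 4% | 4% | 44% | 88% |
| 0.05 | 0.568 | 10% | 12% | 46% | 90% |
| 0.10 | 0.618 | 21% | 26% | 51% | 93% |

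Example: 0.10 / (1 − 0.518) = 0.21 of the residual variance, and 1 / (1 − 0.21) = 1.26.

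**Step 3: the same range read as partial R²**, that is, as a share of what baseline ARAT leaves unexplained. SD = 18 × √(0.482 × (1 − partial R²)), which is 12.37 at 0.02 and 11.85 at 0.10. With the normal approximation, power goes from 43.3% to 44.0–47.1% at 40 per arm and from 87.3% to 87.9–90.5% at 120 per arm. The gain is about 1 to 4 points. Steps 2 and 3 do not conflict: an increment of 0.10 in total R² is a partial R² of 0.21.

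**Step 4: cost if finger extension proves uninformative.** Three levels use two degrees of freedom. The variance penalty is roughly 2/80 = 2.5%, or about 3%, with 80 evaluable, and 2/240 = 0.8% with 240.

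**The case against.** **The covariate set is already sound.** Baseline outcome plus stratification variables is a standard, valid choice. Omitting a further prognostic factor does not bias a randomised comparison in a linear model, and the power claim at 300 holds without it. All of this stands, and it limits the point to efficiency.

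**The gain may be small.** The Limitations text joins low ARAT and absent finger extension with an *or*, while discussing whether therapy should continue. It does not say that finger extension predicts beyond the ARAT. The ARAT is itself largely a test of grasping, and the model holds both the continuous score and the strata. This stands too: the top of the assumed range requires finger extension to explain a fifth of the variance left after the ARAT.

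**Chance imbalance.** A reader might infer that an imbalance in finger extension passes directly into the treatment estimate. Suppose 40 per arm and one third without extension (assumed). The SD of the difference in proportions is √(2 × (1/3) × (2/3) / 40) = 0.105, so a gap of 15 percentage points or more arises in about 15% of trials. With an assumed 10-point prognostic gap, that shifts the estimate by 1.5 points. But ARAT stratification and adjustment remove the shared part, so this is an upper bound on invented inputs. It is also the same residual variance already counted in the power figures, not an extra harm.

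**Secondary outcomes.** These "will be analysed using the same approach as used to test the primary outcome". A reader might infer that they are adjusted for baseline ARAT only, with no baseline of their own. The documents do not support that as an error. The outcome measures are collected at baseline, and the Sample size section says "Using similar assumptions, the study would have 80% power to detect differences between groups of 0.3 SDs", which presupposes a baseline correlation. Own-baseline adjustment (r = 0.72, 120 per arm) gives 92%, and no baseline gives 64%, so each outcome's own baseline is the natural reading. The 80% is claimed for WMFT, MAL and CSI, not for EQ5D-5 L. Covariate lists for each outcome can properly sit in the analysis plan, which is not shown.

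**Conclusion.** The point holds as a modest, optional gain in precision for the primary ARAT analysis. The protocol names finger extension as prognostic, records it before randomisation and uses it to define subgroups, but does not adjust for it.

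Nothing is biased by the omission, and the 80% claim at 300 is safe. The benefit matters more at 100 participants: from about 42% to between 44% and 51% if the R² increment is 0.02 to 0.10, or about 1 to 4 points if that range is the partial R². At 300 the corresponding figures are 87% to 88–93%, or about 1 to 3 points. These sizes rest on the assumed range, on the protocol's SD and correlation, and on 20% loss. Even the best case leaves a trial of 100 near 50% power, so the change does not repair the reduced sample. For the secondary outcomes, nothing more than a clarification of wording is warranted.

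**What to change.** In Statistical analysis, or in the analysis plan before any unblinded analysis, add baseline voluntary finger extension (none, partial, full; Fugl-Meyer item 25) as a pre-specified fixed effect in the overall ARAT model.

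In the same place, state that this term is dropped from the models fitted within finger-extension subgroups. There it is constant and cannot be estimated, and the current text refits the same model in each subgroup.

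Optionally, add one phrase saying that each secondary and tertiary outcome is adjusted for its own baseline value.

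The cost is a few words and two degrees of freedom: about 3% of variance with 80 evaluable and under 1% with 240, if the covariate proves uninformative. No new data are needed.

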### Trial interventions

#### Task-specific intervention

The task-specific intervention will be guided by a detailed protocol (28). The intervention will occur in the participant’s home. In brief, the intervention therapist analyses the whole of the task which is to be trained, e.g., reach-to-grasp., to identify movement components to be prioritised for training and individual movement performance targets to be reached. This will be necessarily different for each participant. The person’s visual attention is directed to regulatory cues in the environment, which are organised to be functionally relevant, individualised and varied, by providing meaningful everyday objects of different sizes, weight and shape, in different positions. The therapist’s role is like a sports coach. He/she uses knowledge of critical biomechanical characteristics of the task to give instructions (by demonstration or verbally) which are concrete and task oriented. Repetitive practice and motor learning principles are used to empower the participant to practice on their own.

Training will be delivered according to an exercise manual containing 142 exercises in words and photographs including variations of the exercises to allow for different levels of difficulty and complexity.

The manual was developed during our previous feasibility trial by a team of therapists during the feasibility trial ([name], [name], [name], [name]) (28) with consultation with user representatives and local specialist neurophysiotherapists. It describes the underlying principles, clinical objectives and individual exercises to achieve the stated objectives. It also details a menu of the treatment strategies (in words and pictures) and includes variations of the treatment strategies to allow for different levels of difficulty and complexity. A description of the development of the manual is available (28), however the manual itself is under embargo until the completion of the trial.

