Participants receive 14 × 1-h visits from a therapist over the 6 weeks (3 visits in weeks 1–3, 2 visits in weeks 4–5, 1 visit during week 6). This will *replace* any usual care training for the upper limb. The intensity of practice within each 1-h session will be dependent on individual participant’s capabilities, but high numbers of repetitions will be encouraged, with the aim of delivering between 100 and 300 repetitions within each 1-h session. Beyond the target of 100–300 reps, participants will do as many repetitions as they can accomplish in 1 h, within limits of fatigue. Any repetition is counted, full range is not required, and repetitions are recorded on a task-specific therapy log form. The number of minutes spent practising each exercise is also recorded on the form, as well as the number of the session (out of 14 sessions), and the total duration of task-specific practice in each session (minutes).

Stretches may be indicated when decreased muscle length is present as a secondary consequence from having had a stroke. When decreased muscle length is interfering with performance of exercises from the task-specific exercise manual, a maximum of 5 min during the 1-h treatment may be spent in stretching and may include short duration stretches of between 8 s to 5 min. Longer duration stretches, of 20–30 min duration, may also be prescribed as part of the patient’s self-managed programme, to be performed outside of their 1 h daily self-practice. Long duration stretches will not be used in the one-to-one treatment sessions with the therapist. The stretches that may be used are described with photographs in a document ‘Upper Limb Stretches’, which is given to the therapists.

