### Who delivers treatment, amount of treatment and adherence

Different therapists will deliver the usual care and task-specific interventions. Usual care will be delivered by the usual clinical service physiotherapists and/or occupational therapists. Task-specific intervention will be delivered by a group of therapists employed to deliver the intervention in the trial. Intervention therapists will be trained to deliver task-specific training over a 2-day course including theory, and practice with participants with stroke, prior to delivering the treatment. Further training sessions with participants with stroke, and/or follow-up discussion about intervention, with the trainer are available, if needed. Therapists will also receive instruction in the importance of strictly following the treatment manual.

The treatment duration for the task-specific intervention will be 6 weeks, with 1-h visits occurring 3 times in the first 3 weeks, twice in each of the next 2 weeks, then once in the final week, (tapered to increase self-management).

For each intervention therapist, fidelity to treatment protocol will be assessed. For each therapist, we will aim to assess fidelity on 4 separate occasions. A treatment fidelity checklist will be used. If fidelity to treatment schedule is <90% then further training will be given within the 2 weeks following the fidelity assessment, until the 90% criteria is achieved.

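### The stated model has no therapist term, so the treatment-effect standard error is understated if task-specific participants who share a trial therapist have correlated outcomes

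*Protocol article*

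**What the plan says.** The section on who delivers treatment separates the staff by arm: "Different therapists will deliver the usual care and task-specific interventions". For the active arm, "Task-specific intervention will be delivered by a group of therapists employed to deliver the intervention in the trial". For the control arm, "Usual care will be delivered by the usual clinical service physiotherapists and/or occupational therapists". Contact in the active arm is substantial: "Participants receive 14 × 1-h visits from a therapist over the 6 weeks". The same section treats the therapist as a unit worth monitoring: "For each intervention therapist, fidelity to treatment protocol will be assessed".

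The Statistical analysis section then sets out the model. On the fixed side, "fixed effects in the model will be group, time and the interaction of time by group, baseline ARAT score and stratification variables", the last of these being site and severity of upper limb impairment. On the random side, "A random effect for subject will be included". The same approach is to be used for the Motor Activity Log, Wolf Motor Function Test, Fugl-Meyer, EQ5D-5L, Caregiver Strain Index and modified Rankin Scale. No therapist term, cluster-robust variance or therapist sensitivity analysis is stated, and the Sample size section makes no allowance for clustering. The article gives neither the number of trial therapists nor a therapist ICC.

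**The concern.** Therapists are nested within arm. In the task-specific arm several participants can share one trial therapist, who analyses the task, sets targets and coaches them through up to 14 one-hour sessions. Usual care is spread over ordinary staff in several kinds of service. This is a partially nested design: outcomes may be correlated within therapist in one arm, with no matching structure in the other.

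A subject random effect absorbs the correlation between one person's 6-week and 6-month scores. It leaves different people independent of each other, including people treated by the same therapist. If therapists differ in their effect on outcome, that variation belongs in the standard error of the group difference, and the stated model leaves it out. The confidence interval is then too narrow and the p-value too small, for the primary outcome and for every secondary outcome analysed in the same way.

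**Working it through.** **Inputs from the article.** Difference 5 ARAT points, SD 18, baseline to follow-up correlation 0.72, 150 per group, 20% loss, two-sided 5% (Sample size); 1:1 allocation (Study methods); revised realistic total of 100 (Modifications due to Covid-19). Evaluable per arm: 150 × 0.8 = 120 as planned, and 50 × 0.8 = 40 at the revised total.

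**Inputs assumed.** Therapist ICC 0 to 0.10 and 4 to 20 therapists. The article gives no value for either.

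**The plan's own figure.** Power = Φ(5 / (SD × √(2/120)) − 1.96).
- Change-score SD = 18 × √(2 × (1 − 0.72)) = 13.47: power 82.0%, close to the stated 80%.
- Baseline-adjusted SD = 18 × √(1 − 0.72²) = 12.49: power 87.3%.
- Unadjusted SD 18: power 57.6%.

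The stated power is approximately reproduced with the change score. None of these calculations contains a therapist design effect.

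**Formula for clustering in one arm.** With m completers per therapist, the design effect in the task-specific arm is DEFF = 1 + (m − 1) × ICC. It is 1 in usual care. The variance of the difference is inflated by (1 + DEFF)/2, the true standard error is √((1 + DEFF)/2) times the model's, and the actual type I error is 2 × (1 − Φ(1.96 / that ratio)).

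**At the revised size (40 evaluable per arm).** Caseloads of 4 to 8 correspond to 40/4 = 10 down to 40/8 = 5 therapists.

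| m | ICC | DEFF | Variance inflation | SE ratio | Type I error |
|---|---|---|---|---|---|
| any | 0 | 1.00 | 1.00 | 1.000 | 5.00% |
| 4 | 0.02 | 1.06 | 1.03 | 1.015 | 5.35% |
| 5 | 0.05 | 1.20 | 1.10 | 1.049 | 6.17% |
| 8 | 0.10 | 1.70 | 1.35 | 1.162 | 9.16% |

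With only 4 therapists (m = 10), ICC 0.01 / 0.05 / 0.10 gives 5.5% / 7.7% / 10.4%.

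**At the planned size (120 evaluable per arm).** Caseloads are larger for the same number of therapists.

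| Therapists | m | SE ratio at ICC 0.01 / 0.05 / 0.10 | Type I error |
|---|---|---|---|
| 6 | 20 | 1.046 / 1.214 / 1.396 | 6.1% / 10.7% / 16.1% |
| 10 | 12 | 1.027 / 1.129 / 1.245 | 5.6% / 8.3% / 11.5% |
| 20 | 6 | 1.012 / 1.061 / 1.118 | 5.3% / 6.5% / 8.0% |

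**Does the fixed site effect remove it?** Data were simulated under no treatment effect, with one follow-up score, therapist effects in one arm and a two-level site term in the model (4,000 replicates per setting). With 120 per arm, 6 therapists and ICC 0.05, the rejection rate was 11.1% (formula 10.7%). With 40 per arm, 10 therapists and ICC 0.05, it was 6.0% (formula 5.9%). At ICC 0 the simulated rates ranged from 4.6% to 5.8%, which shows the simulation noise. The site term removed little. That is to be expected, because it is common to both arms while the therapist effect acts in one.

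**The case against.** **The protocol works to make therapists alike.** It has a manual of 142 exercises, a 2-day course, instruction to keep to the manual, four intended fidelity checks per therapist and retraining below 90%. Only 14 of the 56 hours are therapist-led; the other 42 are self-practice. This stands as a reason to expect a low ICC. It does not show that the ICC is zero.

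**A reader might infer that a small group of therapists treats the whole arm and that the standard errors are therefore certainly wrong.** The documents support neither. The article says only that there is a group of trial therapists, and it lists many services in two states. At 120 evaluable per arm, 4 to 8 completers per therapist would mean 15 to 30 therapists. Inflation depends on an ICC that is not given.

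**Individualised training is weak evidence.** The sentence "This will be necessarily different for each participant" concerns movement components and targets fitted to the person. It describes variation between participants and does not show that patients of one therapist share outcomes. The point rests on shared therapists and repeated contact.

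**The analysis plan may add a therapist term.** It may; it is not shown, and the article does not say that the subject effect is the only random term. But the article spells out the fixed and random parts of the model, so a plan that follows it as written carries the omission forward.

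**Usual-care participants may share clinicians, and task-specific participants may have more than one therapist.** Both are possible. Shared usual-care clinicians would, with a positive ICC in that arm, add to the understatement. Shared trial therapists mean that the remedy needs an assignment rule.

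**Conclusion.** The point holds in conditional form. The design is partially nested, and the stated model ignores correlation between participants who share a trial therapist. For any positive therapist ICC the standard error of the treatment effect is understated and type I error exceeds 5%.

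At the revised total of 100, the effect is modest in the middle of the assumed range: a true standard error about 1.05 times the model's, and type I error of 6.17%. The 9.16% figure needs the high caseload and the high ICC together, so it is an upper value within the assumptions and not a prediction. At the planned size, inflation would be larger if therapists were few. With an ICC of zero there is none. All of these sizes rest on assumed ICCs and therapist numbers. What the article itself establishes is the separation of therapists by arm and the absence of a therapist term from the stated model. The change is worth making because it is cheap and affects the primary outcome and all secondary outcomes analysed with this model.

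**What to change.** In the analysis plan, add a random effect for therapist in the task-specific arm only, treating each usual-care participant as their own cluster, and use a small-sample degrees-of-freedom correction. State the rule for participants seen by more than one trial therapist, for example assignment to the lead therapist. If the term cannot be estimated with few therapists, keep the stated model as primary, report the therapist model as a pre-specified sensitivity analysis, and give the estimated ICC and the number of participants per therapist.

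Therapist identity should be a field in the analysis dataset. The trial already holds it, because the Trial Manager gives task-specific participants their therapist's name (Participant recruitment). The therapy log fields listed under Task-specific intervention do not include it.

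The cost is a few lines of analysis-plan text and one data field. The downside is a slightly wider interval and possible convergence problems. No change to treatment or assessments is needed.

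### The finger-extension subgroup analysis aims at differential effects, but as planned it gives no estimate or confidence interval of the difference between subgroups

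*Protocol article*

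**What the plan says.** All of this stands in the Statistical analysis section of the protocol article. The aim is: "We will conduct sub-group analyses to determine differential effects of the intervention in participants with voluntary finger extension", in three levels assessed at about 3 months after stroke. The method is: "The GLMM regression model described above will be fitted within each of the sub-groups". The model referred to is the one for the primary outcome, in which "fixed effects in the model will be group, time and the interaction of time by group, baseline ARAT score and stratification variables". It contains no term for finger extension. The section then closes off formal testing: "No formal tests of significant interactions will be assessed for these models, since the study is not powered for these tests". No comparison of effects between the subgroups, estimated or tested, appears elsewhere in the article.

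The Abstract says that the mixed model will report mean differences between the groups at each time point with 95% confidence intervals and p-values. The Data collection section shows that finger extension is recorded at baseline through an item of the Fugl-Meyer assessment.

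**The concern.** A differential effect is a difference between subgroup effects. The plan names that as its target but produces only the separate effects, each with its own interval and p-value. With three such results in front of them, readers will naturally note which are significant. That comparison is not valid evidence of effect modification, because significance in one small subgroup and not in another is common when the true effects are identical.

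The factor matters in this trial. The Limitations section explains that people without finger extension were included on purpose, describes that state as predictive of poor recovery, and raises the question of whether continuing therapy in them is justified. A chance pattern of benefit with extension and none without could be read as an answer to that question.

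This is not a detail left to the analysis plan. The protocol fixes the method and excludes the test, and an analysis plan that follows it would inherit the mismatch.

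**Working it through.** **The plan's own figure.** No number is stated for the subgroup analysis. The Sample size section gives "a pooled standard deviation on the ARAT of 18 and a correlation between baseline and follow-up of 0.72", a target of 5 points, two-sided 5%, 300 participants, 20% loss and 80% power. With adjustment for baseline, the residual SD is 18 × √(1 − 0.72²) = 12.49. That gives 98 per arm, or 123 per arm (246 in total) after loss, and 87% power at 120 per arm. A change-score SD of 18 × √(2 × 0.28) = 13.47 gives 286 in total, and 82% power at 120 per arm. The 300 is therefore close to a rounded-up change-score calculation. This is a separate matter, and nothing below depends on it.

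**Inputs for the subgroups.**
- Completers: 300 × 0.8 = 240 as planned. With the 100 recruits given as more realistic in the section on Covid-19 modifications, 100 × 0.8 = 80.
- Allocation 1:1.
- Subgroup shares are not given. Equal thirds are assumed, and a 50/30/20 split is tried as a range.
- Residual SD 12.49 in every subgroup, one time point, no gain from repeated measures.

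**Effect within one subgroup.** SE = 12.49 × √(2/m), with m completers per arm.

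| Completers | m | SE | Power for 5 points (t; normal) | 95% CI half-width (normal; t) |
|---|---|---|---|---|
| 240 | 40 | 2.79 | 42%; 43% | 5.5; 5.6 |
| 80 | 13.3 | 4.84 | 17%; 18% | 9.5; 10.0 |

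**Chance of discordant significance when the true effect is 5 points in all three.** This is 1 − p³ − (1 − p)³.
- 240 completers: p = 0.424, so 1 − 0.076 − 0.191 = 0.733.
- 80 completers: p = 0.167, so 1 − 0.005 − 0.578 = 0.417.

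The normal approximation gives 74% and 44%. With a 50/30/20 split the figures are 75% and 42% (t), or 76% and 44% (normal), so the result does not hinge on equal thirds.

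**The missing quantity.** For the difference between two subgroup effects, SE = √(SE₁² + SE₂²).
- 240 completers: √2 × 2.79 = 3.95; 95% CI ± 1.96 × 3.95 = ±7.7 points; power 24% for a 5-point and 72% for a 10-point difference.
- 80 completers: √2 × 4.84 = 6.84; ±13.4 points; power 11% and 31%.
- Contrasting subgroups with 50% and 20% shares: ±8.4 and ±14.5 points.

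**The case against.** Four points can be made for the plan.

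- **The protocol is right about power.** At 24% or 11% for a 5-point difference, a formal interaction test would usually be uninformative, and declining one in an exploratory analysis is acceptable. A reader might infer that separate fits have even less information than the interaction. The figures show the reverse: the contrast is less precise than each subgroup effect (SE 3.95 against 2.79 at 240 completers). This stands, but it justifies an exploratory label rather than leaving the contrast out.
- **Only formal tests are excluded.** A reader might infer that the plan forbids an interaction estimate, or cannot answer its own question. The text does not say that. The Abstract promises mean differences with confidence intervals, and the subgroups do not overlap, so anyone could subtract the estimates and combine the standard errors. This stands too. The gap is that no such contrast is planned.
- **Separate fits have a rationale.** They let residual variance and the baseline slope differ by subgroup. That is sensible for a bounded score (0 to 57) and a factor tied to recovery, and the remedy should keep the option open.
- **The protocol does not propose comparing p-values or selecting patients.** That is correct. The discordance figures describe a foreseeable misreading, not a planned decision rule.

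What remains is the mismatch between aim and method. Rewording the aim as descriptive would remove it on paper, but would leave readers with the same three results side by side.

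**Conclusion.** The point holds in a limited form. The stated aim is a difference in effects, and the planned analysis delivers neither an estimate nor an interval for it. Under a uniform 5-point effect, the subgroup results would differ in significance about 73% of the time at 240 completers and 42% at 80.

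These figures assume equal thirds (similar under 50/30/20), whole-sample SD and correlation applied unchanged within each subgroup, and a single time point. The SD and correlation could well differ by finger extension. That would move the percentages, but not the finding that no contrast is planned.

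The documents do not support the stronger claims that an interaction estimate is ruled out or that the low-power statement is wrong. The primary analysis is unaffected. The change should be made before analysis because it is cheap and concerns the only pre-specified subgroup question.

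**What to change.** On the full intention-to-treat set, add finger extension and its interaction with group (by time) to the model, letting residual variance differ by subgroup if needed. Equivalently, keep the separate fits and contrast their estimates, combining the standard errors as above.

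Report the three week-6 effects and the between-subgroup differences with 95% confidence intervals, labelled exploratory. State that any claim of differential effect rests on the contrast and not on significance within subgroups. The sentence on low power for a formal test may stay. An interaction p-value and a one-degree-of-freedom trend across the three levels are optional.

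The cost is a few sentences in the protocol or analysis plan and a few lines of code. No new data are needed, since finger extension is already recorded at baseline. The drawback is a wide interval, about ±7.7 points at 240 completers and ±13.4 at 80 for two equal-third subgroups, which is an honest statement of what the trial can say.
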